# A development study and randomised feasibility trial of a tailored intervention to improve activity and reduce falls in older adults with mild cognitive impairment and mild dementia

**DOI:** 10.1186/s40814-018-0239-y

**Published:** 2018-02-17

**Keywords:** Dementia, Activities of daily living, Therapeutic exercise, Occupational therapy, Physiotherapy, Falls, Randomised controlled trial, Adherence, Economic evaluation, Process evaluation

## Abstract

**Background:**

People with dementia progressively lose abilities and are prone to falling. Exercise- and activity-based interventions hold the prospect of increasing abilities, reducing falls, and slowing decline in cognition. Current falls prevention approaches are poorly suited to people with dementia, however, and are of uncertain effectiveness. We used multiple sources, and a co-production approach, to develop a new intervention, which we will evaluate in a feasibility randomised controlled trial (RCT), with embedded adherence, process and economic analyses.

**Methods:**

We will recruit people with mild cognitive impairment or mild dementia from memory assessment clinics, and a family member or carer. We will randomise participants between a therapy programme with high intensity supervision over 12 months, a therapy programme with moderate intensity supervision over 3 months, and brief falls assessment and advice as a control intervention. The therapy programmes will be delivered at home by mental health specialist therapists and therapy assistants. We will measure activities of daily living, falls and a battery of intermediate and distal health status outcomes, including activity, balance, cognition, mood and quality of life. The main aim is to test recruitment and retention, intervention delivery, data collection and other trial processes in advance of a planned definitive RCT. We will also study motivation and adherence, and conduct a process evaluation to help understand why results occurred using mixed methods, including a qualitative interview study and scales measuring psychological, motivation and communication variables. We will undertake an economic study, including modelling of future impact and cost to end-of-life, and a social return on investment analysis.

**Discussion:**

In this study, we aim to better understand the practicalities of both intervention and research delivery, and to generate substantial new knowledge on motivation, adherence and the approach to economic analysis. This will enable us to refine a novel intervention to promote activity and safety after a diagnosis of dementia, which will be evaluated in a definitive randomised controlled trial.

**Trial registration:**

ClinicalTrials.gov: NCT02874300; ISRCTN 10550694.

## Background

Dementia is a syndrome of progressive and usually irreversible loss of memory and other cognitive functions including agnosia, apraxia, language and executive function, caused by a variety of brain diseases, and severe enough to interfere with daily function. Mild cognitive impairment (MCI) is defined by measureable memory loss or other cognitive decline in the absence of interference with daily function, but which progresses to dementia in about half of cases. Dementia affects 1% of those at age 65, 20% at age 80 and 30% or more at age 90. Prevalence in the UK is about 850,000, and expected to double by 2030 [1].

There is no cure for dementia, but acetylcholinesterase inhibitor drugs and cognitive stimulation therapy can improve cognition by a modest amount [2, 3]. There are few other interventions to maintain or improve health status. Two potential mechanisms for avoidable deterioration in cognition and function are crises associated with physical health problems (such as falls and their consequences), and progressive restriction of activity by the person with dementia or those who support and care for them, often with the goal of maintaining safety.

A fall is defined as unintentionally coming to rest on the floor or at a lower level, through whatever cause [4]. People with dementia and MCI are at high risk of falling with at least a twofold increased risk compared with cognitively normal older people [5–7]. This equates to an annual fall incidence of 60–80% [8–11]. Consequences of falls include fractures, other injuries, hospital attendance, the ‘fear of falling syndrome’, immobility and loss of independence. People with dementia also have a higher risk of fractures, hip fractures in particular, and poorer outcomes after fracture, compared with people who are cognitively intact [6, 12]. Up to a third of emergency hospital admissions occur in an older person with dementia, and over half of these are associated with a fall [13]. Each year, in the UK, there are 75,000 hip fractures, set to rise by half again in the next 10 years, and 200,000 other fragility fractures. The combined cost of these is over £2 billion per year, and use 1.6 million hospital bed days. Half of hip fractures occur in someone with dementia [14].

There has been extensive research into falls prevention in older people. Risk factors are muscle weakness, neurological disease, medications, poor vision and environmental factors. Multi-factorial interventions reduce risk [15, 16] but these interventions have not been shown to reduce falls in people with dementia or MCI [8, 17–19]. A systematic review of interventions concluded that they were poorly adapted to the needs of people with dementia [20]. Falls guidelines recommend that cognitive function is assessed, but do not say how to respond [21]. People with dementia have more ‘conventional’ falls risk factors than people of similar age without dementia [8]. They also have dementia-specific risk factors including: type and severity of dementia, specific cognitive and gait deficits, behavioural disturbances, and psychotropic drug use [11, 22, 23]. Studies highlight the importance of attention, and dual-task cost (increased risk when concentrating on two things at once) [24], manifestations of impaired executive function (ability to form, maintain, and shift mental set [25]). Abnormalities in executive function and gait are associated with falls [26, 27]. Dual-task and gait abnormalities are found early in dementia [11, 28–31] and MCI [32] beyond what would be considered ‘normal ageing’.

Potentially reversible risk factors provide opportunities to intervene before inevitable deterioration occurs. Systematic reviews have considered the impact of strength and balance training in older people, with and without dementia [19, 33–37]. Moderate-intensity exercise, 2–3 times a week, improves strength, gait speed, and ability in activity of daily living [38–42]. There may be additional benefit in slowing cognitive decline [38, 41, 43–47] although the size of this effect appears small. Training can improve executive function, dual-task performance and gait parameters [48–52]. Functionally orientated therapy can improve ability to perform activities of daily living [44, 53, 54]. There is insufficient evidence to confirm reduction in falls, improved mood or behaviour for people with dementia, or reduced carer strain [19, 20, 38, 40, 45, 55]. Customary levels of physical activity are low among older people [56].

The FINALEX trial of 12 months of twice-weekly, supervised exercise at home for people with established dementia and their co-resident spouse, reduced deterioration in activities of daily living and halved the rate of falling, from 3.1 to 1.4 falls per person-year [57]. Hospital admissions and overall costs were reduced. This demonstrates that intensive exercise is achievable, sustainable with the right support, and cost-effective. The challenge is how to achieve sufficient participation, adherence and persistence in the NHS and UK cultural environment, and to be inclusive, for example, of the 50% of people with early dementia who live alone.

A new intervention must lead to changes in individuals that are physiologically and neuro-psychologically credible, but must also take account of aspects of behaviour change [58–61]. The utility of current approaches to behaviour change (e.g. behaviour change wheel [58]) in the context of dementia is unknown, but provides a framework for further investigation. Barriers to sustaining a moderate to vigorous exercise programme include not perceiving oneself as being at risk from falls; perceived lack of relevance of exercise or other interventions; and focus on priorities such as maintaining independence, or family, social or domestic concerns [62–64]. Barriers to long-term adherence include forgetfulness, medical co-morbidities, planning problems and practical support. Motivational strategies might include supervision, tailoring, remote feedback, prompts, memory aids, goal setting, and rote-learning habit formation [65–72]. This problem has been studied in other conditions; for example, adherence to exercise in chronic musculo-skeletal pain [71], but overall evidence is sparse. It is not clear which, if any, strategies are acceptable and effective for people with dementia.

## Methods

### Aim

This research aims to develop and test a novel intervention to maintain activity and reduce falls in older adults with MCI and mild dementia.

The feasibility study aims to answer practicability and feasibility questions about recruitment and retention of participants, study procedures, delivery, intensity and burden of intervention, adherence, data collection and completion of outcomes measures, and implementation of a rehabilitation staff training programme to ensure that a planned large-scale trial is successful.

We will study how to maximise participant adherence with the programme, developing practical strategies to optimise adherence, and ascertaining in retrospect what did and did not work for particular individuals, both during the therapy programme and in the long term.

We will undertake a process evaluation, studying fidelity, understanding mechanisms and context, including barriers and facilitators to participation.

We will collect resource-use data to enable preliminary economic modelling.

### Study design

A two-centre, pragmatic, parallel group, feasibility RCT will be conducted (Figs. 1 and 2). After informed consent, participants will be randomised to one of two intervention arms (high- or moderate-intensity supervision) or a control group who will receive standard falls assessment and advice. Where possible, each participant will nominate a family member, friend or carer to be both an informant and a participant in their own right. A process evaluation [73], study of motivation and adherence, and a preliminary economic analysis will be undertaken, using mixed qualitative and quantitative methods.

### Setting

Recruitment will be from locality-based, secondary-care memory clinics, and therapy delivered in the participant’s home.

### Participants (inclusion, exclusion, withdrawal)

Eligible patient participants will be aged over 65 years and will have a diagnosis of mild dementia or MCI (of any subtype), attendance at a memory assessment service, or on the ‘Join Dementia Research’ register (a national initiative to encourage participation in dementia research [74]) with a cognitive score ranging 15–25 on the Montreal Cognitive Assessment (MoCA) [75], 18–26 on the standardised Mini-Mental State Examination (sMMSE) [76], or 60–90 on the Addenbrooke’s Cognitive Examination (ACE-III) [77].

Patient participants must be able to walk without human help, able to communicate in English, and to be able to see, hear and have dexterity sufficient to perform neuropsychological tests. Patient participants must have capacity to give consent to participate, and provide written informed consent. Capacity will be assessed and consent taken by a research assistant.

Exclusion criteria for patient participants include comorbidity preventing participation (e.g. severe breathlessness, pain, psychosis, Parkinson’s disease, or other severe neurological disease), life expectancy of less than 1 year, or being unlikely to undertake the intervention regularly (e.g. planned elective surgery, planning to move away, or commitments elsewhere).

Individual participants will discontinue participation if: they withdraw consent or no longer wish to take part; the therapist overseeing their care decides the participant is no longer able to take part (for example due to inter-current illness or injury, progression of their disease or inability to adhere despite adjustment and tailoring of the programme); otherwise at the discretion of the investigator (e.g. risk to safety of staff). Participants may opt not to take part in individual therapy sessions or a series of sessions (e.g. because of holidays or intercurrent illness) without withdrawing from the study. We will collect outcome data from those who withdraw if they are willing.

No formal sample size was calculated for the feasibility study; however, a sample size of 60 was considered sufficient to answer feasibility questions and enable the conduct of the adherence and process of evaluations.

Carer participants will be partners, family members or others in a caring relationship, who are in contact with the patient participants most weeks, are willing to take part and can communicate in English.

For the ‘optimising engagement and adherence’ and process evaluations, we will conduct interviews and focus groups. We will undertake three small focus groups with patients with mild dementia, and their family carers, each comprising three to five participants to investigate promotion of adherence. In the process evaluation, we will conduct semi-structured interviews with about ten participants in each active-treatment arm (moderate- and high-intensity supervision). Carers will be interviewed separately or together with the participant, depending on their preference. We will select for interview participants with low- and high-adherence, identified through their exercise diaries, self-report or therapist-report. We will also seek to interview a sample of participants who discontinue the intervention (up to 10, and their carers). We will undertake two to three staff focus group discussions, each of six to eight members.

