**Fig. 1 Fig1:**
[figure not shown]
Overview of assessment and intervention. *PT* physiotherapist, *OT* occupational therapist, *GP* general practitioner/family doctor, *wk.* week

The control arm will be the offer of a standard falls assessment and advice completed by a therapist, with up to two follow-up visits if thought clinically necessary.

The moderate-intensity supervision arm participants (3-month programme) will receive a total of 11 treatment sessions: 6 from an occupational therapist (OT) and 5 from a physiotherapist over 12 weeks. Participants will be expected to exercise and complete activities independently between supervised sessions, and taught to continue after the supervision period has stopped. The moderate-intensity intervention was modelled on the intervention in an ongoing Australian trial [96, 97].

The higher-intensity supervision arm (12-month programme) will comprise 11 treatment sessions from registered therapists: 6 from an occupational therapist, 5 from a physiotherapist plus supervised support from a rehabilitation support worker (RSW) twice a week for 3 months, once a week for 3 months, once a fortnight for 3 months, and once a month for 3 months. In total they will get 51 treatment sessions, and will be asked to continue with the intervention programme independently as supervision tapers. At initial, review and progression points, the RSW will visit jointly with the therapists.

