#### Efficacy analysis

Descriptive statistics (e.g. means, medians, proportions, standard deviations and ranges) of baseline demographic, health status and service use data will be calculated for each trial treatment arm.

We will compare changes in health status outcomes between the three trial arms.

The Disability Assessment for Dementia and Nottingham Extended ADL scale outcomes will be compared using an analysis of covariance to adjust for the baseline score and stratifying variables. The nature of the distribution of the falls data will also be examined to determine how best to analyse the falls data in the main trial. Statistical analysis will be performed on an intention-to-treat basis. There will be no imputing of missing data. Assumptions in determining the sample size of the main trial will be checked.

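### The withdrawal rule lets a therapist's decision end study participation rather than therapy alone, so any resulting outcome loss may be informative and unequal by arm

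*Protocol article*

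**What the plan says.** In the protocol article, the section Participants (inclusion, exclusion, withdrawal) opens its withdrawal rule with "Individual participants will discontinue participation if: they withdraw consent or no longer wish to take part". It then adds a second route: "the therapist overseeing their care decides the participant is no longer able to take part". The examples for that route are intercurrent illness or injury, and "progression of their disease or inability to adhere despite adjustment and tailoring of the programme". Investigator discretion is a third route.

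Two further sentences in the same paragraph qualify the rule. One separates missed sessions from withdrawal: "Participants may opt not to take part in individual therapy sessions or a series of sessions" without this counting as leaving the study. The other reads "We will collect outcome data from those who withdraw if they are willing".

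Under Intervention, in the text after Fig. 1, the control arm is offered one falls assessment "with up to two follow-up visits if thought clinically necessary". The moderate-intensity arm has 11 sessions over 12 weeks. The high-intensity arm has 51 sessions over 12 months, including visits by rehabilitation support workers. The Blinding section accepts that therapists cannot be blinded.

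The Efficacy analysis section states: "Statistical analysis will be performed on an intention-to-treat basis. There will be no imputing of missing data". The Feasibility analysis section defines retention in a single line as the proportion who complete both the therapy programme and the study follow-up.

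**The concern.** What the rule ends is participation. The next sentence contrasts it with missing sessions while staying in the study, and the one after that refers to the people affected as having withdrawn. The natural reading is therefore that a therapist's decision takes a person out of the study, even though that person has not withdrawn consent. Outcome data then depend on a fresh expression of willingness.

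Three features make this matter statistically. The decision is taken by staff who know the allocation. Its opportunity to operate differs by arm. Its grounds (progression, injury, inability to adhere) relate to the activities-of-daily-living, falls and adherence outcomes. If some of the people stopped give no further data, the active arms lose participants whose outcomes may differ from the rest, and nothing in the analysis restores them.

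The same lack of separation affects retention, which is part of the main analysis. Read as one proportion, it cannot show whether a trial of this kind loses people from therapy, from follow-up or from both. A feasibility study needs that distinction when planning a definitive trial.

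**Working it through.** The article gives no dropout rate, standard deviation or effect size, so there is no stated figure to reproduce. The check has three parts.

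**1. Opportunity for the rule to act**

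| Arm | Contacts | Ratio to control |
|---|---|---|
| Control | 1 assessment + up to 2 visits = at most 3 (taking the assessment as one visit) | 1 |
| Moderate intensity | 11 | 11/3 = 3.7 |
| High intensity | 51, of which 11 are described as from registered therapists | 51/3 = 17 |

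The non-adherence ground presupposes a tailored programme, which only the two active arms have. Illness, injury and progression can arise in any arm, but in control a therapist has few occasions to act on them. The Adverse events section already accepts that unequal staff contact distorts comparison between arms in the reporting of such events.

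**2. Possible shift in an active-arm mean**

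Let f be the share of an arm stopped by the therapist, u the share of those who then give no outcome data, and D the gap in SD units between observed and missing participants. The missing share is q = f × u. The mean over everyone randomised is

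(1 − q) × m + q × (m − D) = m − qD,

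where m is the mean of those observed. The available-case mean is therefore off by f × u × D. All three inputs are assumptions. With 60 participants randomised 1:1:1, each arm has 60/3 = 20.

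| f | u | D (SD) | Missing of 20 | Shift (SD) |
|---|---|---|---|---|
| any | 0 | any | 0 | 0 |
| 10% | 50% | 0.5 | 1 | 0.10 × 0.50 × 0.5 = 0.025 |
| 10% | 50% | 1.0 | 1 | 0.10 × 0.50 × 1.0 = 0.05 |
| 20% | 50% | 1.0 | 2 | 0.20 × 0.50 × 1.0 = 0.10 |
| 20% | 100% | 1.0 | 4 | 0.20 × 1.00 × 1.0 = 0.20 |

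The last row would apply only if no stopped participant gave data, which the protocol does not plan for. For scale, the unadjusted standard error of a difference between two arms of 20 is √(2/20) = 0.32 SD. A shift of 0.05 to 0.10 SD is 0.05/0.32 = 0.16 to 0.10/0.32 = 0.31 of that.

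**3. Retention**

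Suppose 2 of 20 in an active arm are stopped by the therapist and both complete the 12-month visit, with no other loss. Therapy completion is 18/20 = 90% and follow-up completion is 20/20 = 100%. A single proportion requiring both is 90%, and it hides that follow-up was complete.

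**The case against.** The strongest reply is that the safeguard stands in the same paragraph: outcome data are to be sought from willing withdrawers. All data collection in a consented trial depends on willingness, and the proposed change keeps that limit. A reader might infer that the rule defeats the intention-to-treat analysis. The documents do not support this. A therapist's decision does not by itself remove anyone from analysis, and analysing available data by allocated arm without imputation is compatible with intention-to-treat, though exposed to informative loss.

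Other tempting readings also go too far:

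- **That the rule acts almost only in the active arms.** This fits the non-adherence ground. The other grounds can arise in any arm, and no rates are given.
- **That ordinary non-adherence triggers it.** Missing a series of sessions is expressly allowed, and adjustment and tailoring come first.
- **That adherence will be inflated.** This needs stopped participants to leave the denominator, and the Feasibility analysis section excludes nobody.
- **That retention is made artificially low.** Under the stated definition, stopping therapy is a genuine feasibility result. The problem is that two results are merged.
- **That the falls comparison is biased in favour of therapy.** The Efficacy analysis section plans to examine the falls distribution, not to test falls between arms, and the direction of any loss is not established.

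The rule can also be read as ending therapy only. The paragraph on interviews speaks of people who discontinue the intervention, the Follow-up section gives the 12-month visit to researchers, and the Feasibility analysis section reports reasons for non-treatment and for withdrawal as distinct items. These points make the wording ambiguous rather than settled, but they do not remove the gap. The authors had the narrower term and did not use it in the rule, and nowhere do they say that follow-up continues by default after a therapist's decision.

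The comparison of arms is also secondary here, since the main analysis is of feasibility. That limits the weight of the bias in the arm means, but not the point about retention.

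**Conclusion.** The concern holds in a limited form, and the change should be made. The rule as written ends participation on an unblinded decision, on grounds related to outcome, with unequal opportunity by arm. The consequence is limited to people who are stopped and then give no data.

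Its size cannot be known from the documents. It is zero if all of them give data. It is 0.05 to 0.10 SD in an active-arm mean if 10-20% are stopped, half give no data and they differ from the rest by 1 SD. All of these inputs are assumed, and the figure carries over to a between-arm difference only if control has no similar loss. Against a standard error of about 0.32 SD, this is secondary for the preliminary health-status comparisons.

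The firmer reason to act is feasibility. Therapy completion and follow-up completion are separate inputs to the definitive trial, and the plan merges them both in the rule and in the retention measure.

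**What to change.** In the withdrawal paragraph, state that a therapist's decision stops the intervention only. Add that diaries, monthly calls and the 12-month visit continue by default in all arms unless the participant declines data collection.

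In the Feasibility analysis section, replace the single retention proportion with two, completion of therapy and completion of follow-up, each by arm and with everyone randomised in the denominator. Use the same denominator for adherence.

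The clinical criteria for stopping therapy stay with the investigators and are not questioned here.

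The cost is revised wording in the protocol, and in the participant information where it describes withdrawal, plus a few additional follow-ups by procedures that researchers already carry out.
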